# The effect of continuing versus withholding angiotensin-converting enzyme inhibitors/angiotensin II receptor blockers on mortality and major adverse cardiovascular events in hypertensive patients undergoing elective non-cardiac surgery: study protocol for a multi-centric open-label randomised controlled trial

**DOI:** 10.1186/s13063-022-06616-y

**Published:** 2022-08-17

**Keywords:** ACE inhibitors, ARB, Acute kidney injury, Angioedema, Complications, Mortality, Outcomes

## Abstract

**Background:**

Angiotensin-converting enzyme inhibitors (ACEIs)/angiotensin receptor blockers (ARBs) are commonly prescribed to patients with hypertension. These drugs are cardioprotective in addition to their blood pressure-lowering effects. However, it is debatable whether hypertensive patients who present for non-cardiac surgery should continue or discontinue these drugs preoperatively. Continuing the drugs entails the risk of perioperative refractory hypotension and/or angioneurotic oedema, while discontinuing the drugs entails the risk of rebound hypertension and myocardial ischaemia. The aim of this study is to evaluate the effect of continuation vs withholding of ACEIs/ARBs on mortality and other major outcomes in hypertensive patients undergoing elective non-cardiac surgery.

**Methods:**

The continuing vs withholding of ACEIs/ARBs in patients undergoing non-cardiac surgery is a prospective, multi-centric, open-label randomised controlled trial. Two thousand one hundred hypertensive patients receiving ACEIs/ARBs and planned for elective non-cardiac surgery will be enrolled. They will be randomised to either continue the ACEIs/ARBs including on the day of surgery (group A) or to withhold it 24–36 h before surgery (group B). The primary endpoint will be the difference in the composite outcome of all-cause in-hospital/30-day mortality and major adverse cardiovascular and non-cardiovascular events. Secondary endpoints will be to evaluate the differences in perioperative hypotension, angioneurotic oedema, myocardial injury, ICU and hospital stay. The impact of the continuation vs withholding of the ACEIs/ARBs on the incidence of case cancellation will also be studied.

**Discussion:**

The results of this trial should provide sufficient evidence on whether to continue or withhold ACEIs/ARBs before major non-cardiac surgery.

**Trial registration:**

Clinical Trials Registry of India CTRI/2021/01/030199. Registered on 4 January 2021

**Supplementary Information:**

The online version contains supplementary material available at 10.1186/s13063-022-06616-y.

## Background

Annually, more than 280 million people undergo non-cardiac surgery [1]. The mortality rate following non-cardiac surgery is 0.3% [2]. This risk is higher in patients with ischaemic heart disease, diabetes and hypertension. The perioperative period is the most vulnerable period to develop cardiac or vascular complications which are seen in 25% of patients undergoing major abdominal, vascular and orthopaedic surgeries [2]. More than 1/3 of the patients coming for non-cardiac surgery who present with hypertension may be receiving angiotensin-converting enzyme inhibitors (ACEIs)/angiotensin II receptor blockers (ARBs) which are commonly prescribed as first-line anti-hypertensive medications, the advantage being that these drugs modulate the renin-angiotensin-aldosterone axis and are considered cardioprotective [3]. In addition, ACEIs/ARBs are also used to treat patients with chronic left ventricular dysfunction and those with diabetic nephropathy. However, blunting of the renin-angiotensin-aldosterone axis may cause hypotension during induction of anaesthesia [3].

Continuation of ACEIs/ARBS in the perioperative period is associated with intraoperative and postoperative hypotension, and thus, many clinicians choose to withhold administration of these drugs [4]. However, this is often based on individual practice and has no relation to the profile of the patient and/or the surgery performed [3]. In addition, there is variation in practice with regard to the time of discontinuation with some clinicians discontinuing the drugs 24 h before surgery while some others choose to skip a morning dose of the drug. This in turn is not related to the pharmacokinetic or pharmacodynamic properties of the drugs. Other evidence points to the beneficial effects of a continuation of these drugs in the perioperative period with the demonstration of improved outcomes [5]. While perioperative hypotension is certainly a concern with the continuation of ACEIs/ARBs, discontinuation of these drugs before surgery makes patients susceptible to postoperative hypertension when the effects of anaesthetics wear off, and this may cause harm by increasing the risk of myocardial ischaemia [6]. In fact, postoperative hypertension is more frequently seen in those with preoperative hypertension and is known to increase the risk of occurrence of major adverse cardiovascular events [7].

This trial is thus planned to study the effect of continuing vs withholding the ACEI/ARBs on mortality and other major outcomes in hypertensive patients undergoing elective non-cardiac surgery.

## Study hypothesis

A previous retrospective study had found that withholding ACEIs/ARBs 24 h before non-cardiac surgery is associated with a reduction in all-cause mortality [3]. With this background, the primary hypothesis is that discontinuation of ACEIs/ARBs > 24 h before surgery will result in a lower all-cause 30-day mortality and major adverse cardiovascular and non-cardiovascular events. The secondary hypothesis is that there will be a decreased incidence of adverse events like intraoperative hypotension, angioneurotic oedema, and myocardial injury in patients in whom the ACEIs/ARBs are discontinued, and there would be shorter ICU and hospital stay duration. The impact of withholding of ACEIs/ARBs on case cancellations due to rebound hypertension will also be evaluated.

## Objectives

The primary objective of this study is to evaluate the effect of continuing vs withholding of ACEIs/ARBs on the composite all-cause mortality, major adverse cardiovascular outcomes (acute myocardial infarction, stroke, arrhythmias requiring intervention, hypertensive crises, acute pulmonary oedema, postoperative cardiogenic shock), acute kidney injury, postoperative respiratory failure, sepsis and unplanned ICU admissions in hypertensive patients undergoing major non-cardiac surgery. The secondary objective will be to evaluate the incidence of intraoperative hypotension, myocardial injury, angioneurotic oedema, case cancellations and duration of ICU and hospital stay.

## Methods

### Study design

Continuing vs withholding ACEIs/ARBs is a multi-centric, open-label, randomised controlled two-arm trial, with a 1:1 allocation of hypertensive patients undergoing major non-cardiac surgery to either continue or stop their ACEIs/ARBs. When admitted to the hospital, patients will be randomised to either continue their ACEIs/ARBs including on the day of surgery (group A) or discontinue the drugs 24–36 h before surgery (group B). The primary endpoint will be a composite outcome of all-cause 30-day mortality, major adverse cardiovascular events (acute myocardial infarction, stroke, arrhythmias requiring intervention, hypertensive crises, acute pulmonary oedema, postoperative cardiogenic shock), acute kidney injury, postoperative respiratory failure, sepsis and unplanned ICU admissions. The Standard Protocol Items: Recommendations for Interventional Trials (SPIRIT) checklist is provided in Additional file 2, and the schedule of the participant enrolment in the study (SPIRIT figure) is shown in Fig. 1.

**Fig. 1 Fig1:**
[figure not shown]
SPIRIT figure

### Settings

The trial will be conducted in three tertiary care hospitals in India: All India Institute of Medical Sciences Bhubaneswar, JIPMER Puducherry and CMC Vellore. All three centres are high-volume centres and have dedicated anaesthesiologists caring routinely for patients with various co-morbidities undergoing non-cardiac surgery.

### Participants

We aim to enrol 2100 adult hypertensive patients undergoing elective major non-cardiac surgery under general or neuraxial anaesthesia over a period of 3 years (Fig. 2). Eligible patients will be screened and enrolled during their preoperative visit, and the project staff will follow up with the patient before surgery to ensure randomisation and compliance with the group allocation. Patients who are allocated to group A (continuing the ACEIs/ARBs) will continue to take these medications as per schedule including the day of surgery. For those who are allocated to group B (discontinuing the ACEIs/ARBs), these drugs will be omitted 24–36 h prior to surgery. Patients will then be followed up in-hospital by the investigators and at 30 days by telephonic calls by the project staff.

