### Randomisation and blinding

All study patients will receive the same standards of care and management, including treatment of any harm resulting from the trial. However, they will receive no compensation as a result of participation in the study. They will be randomised to either continue with their ACEI/ARB treatment (including on the day of surgery) (group A) or to withhold it 24–36 h before surgery (group B) (two doses of the ACEI or ARB will be omitted to account for variation in the timing of administration, i.e. morning or evening). The patient’s blood pressure will be monitored periodically and treated with calcium channel blockers if necessary. Other antihypertensives that the patient may be concurrently receiving will be continued on the day of surgery. All such orders will also be recorded. Following surgery, anti-hypertensive medications including ACEIs/ARBs will be restarted at the earliest and the date of restarting anti-hypertensive therapy will be noted.

Randomisation will be carried out using permuted block randomisation (blocks of 20). The randomisation codes and sequence will be computer-generated by a statistician at each institute. The randomisation codes and the sequence will be kept secure at each participating centre. One code from a block sequence will be allotted each time when the patient is enrolled into the study. Allocation concealment will be with opaque sealed envelopes which will be opened 2 days before surgery. The diagnosis of outcomes will be made by clinicians treating the patients. The data for primary and secondary outcomes will be collected from the anaesthesia and surgical case records by the investigators and the project staff. The project staff will be trained by the investigators in the aspects of data collection and approach to missing data.

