### Efficacy end-points

The composite primary outcome and the secondary outcomes will be collected for each patient. Diagnosis of complications will be made by the treating physicians. A data adjudication committee will review the appropriateness of the collected data for each outcome measure. Members of the committee will be blinded to the group allocation and comprise non-participating clinicians from each centre.

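### The protocol gives project staff both the preoperative allocation check and the 30-day telephone follow-up, and does not mask or separate the callers, so post-discharge non-fatal events may be elicited by someone who knows the arm

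*Protocol article*

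**What the plan says.** All references are to the protocol article.

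- **Study design** describes a "multi-centric, open-label, randomised controlled two-arm trial, with a 1:1 allocation".
- **Participants** gives the project staff two tasks. Before surgery, "the project staff will follow up with the patient before surgery to ensure randomisation and compliance with the group allocation". After surgery, "Patients will then be followed up in-hospital by the investigators", and then "at 30 days by telephonic calls by the project staff".
- **Randomisation and blinding** states: "The diagnosis of outcomes will be made by clinicians treating the patients". Data for the primary and secondary outcomes are "collected from the anaesthesia and surgical case records by the investigators and the project staff".
- **Efficacy end-points** provides a data adjudication committee that reviews whether the collected data are appropriate. "Members of the committee will be blinded to the group allocation". This is the only masking of outcome assessment that the article states.
- **Data collection and follow-up** adds that investigators will contact discharged patients or their next of kin to retrieve missing data. It does not mask that contact either.
- **Objectives** and **Study design** list a composite of death, several cardiovascular events, acute kidney injury, respiratory failure, sepsis and unplanned ICU admission. The 30-day window is attached explicitly to mortality only, and the article does not say which components the call collects.

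**The concern.** Checking that a patient keeps to the allocated arm cannot be done without knowing the arm. If the person who made that check also makes the 30-day call, how hard they probe, or how readily they accept a vague answer, can depend on the arm. Study hypothesis states a direction: withholding should give fewer events. Unequal elicitation could therefore push the primary comparison towards that hypothesis, although it could also run the other way.

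The committee gives one-sided protection. An event that is recorded too readily can be rejected on masked review. An event that the caller did not elicit never reaches the committee. The exposed part is non-fatal primary events after discharge that no hospital record at the centre would show. Several components, such as suspected sepsis or an arrhythmia that needed intervention, could be reported to a caller in this way.

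**Working it through.** **Who does what, and who is masked**

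| Step | Done by | Masking stated |
|---|---|---|
| Preoperative allocation check | Project staff | No; needs the arm |
| Diagnosis of outcomes | Treating clinicians | No |
| Outcome data from case records | Investigators and project staff | No |
| 30-day call | Project staff | No |
| Retrieval of missing data after discharge | Investigators | No |
| Review of collected data | Adjudication committee | Yes |

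**The plan's own figure**

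Inputs from Sample size calculation: 25% in the reference group, a 21% relative decrease (0.25 × 0.79 = 19.75%, a difference of 5.25 points), 80% power, final alpha 0.048 (taken as two-sided; the article does not say), 1:1 allocation.

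n per arm = [1.977 × √(2 × 0.22375 × 0.77625) + 0.842 × √(0.25 × 0.75 + 0.1975 × 0.8025)]² / 0.0525² ≈ 1001, so 2002 in total. The stated 2016 agrees within 1%, and 2016 patients give 80.3% power. Masking the caller changes neither the sample size nor alpha.

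**Illustration of the possible bias**

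The article gives neither the share of patients whose first primary event comes after discharge and is found only by the call, nor any difference in pick-up. Both are assumptions here.

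- Bias in the risk difference = share × difference in pick-up.
- Standard error with 1008 per arm at 25% = √(2 × 0.25 × 0.75 / 1008) = 1.93 points.
- With no true effect, rejection probability = 1 − Φ(1.977 − bias/SE) + Φ(−1.977 − bias/SE).

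| Share of patients | Pick-up gap (points) | Bias (points) | Bias / 5.25 | False-positive rate |
|---|---|---|---|---|
| 0% | any | 0 | 0% | 4.8% |
| 3% | 10 | 0.3 | 6% | 5.1% |
| 5% | 20 | 1.0 | 19% | 7.9% |
| 8% | 20 | 1.6 | 30% | 12.8% |
| 8% | 30 | 2.4 | 46% | 23.2% |

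Middle row: 0.05 × 0.20 = 0.010; 1.0/1.93 = 0.52; 1 − Φ(1.46) + Φ(−2.50) ≈ 0.079.

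Shares of 3%, 5% and 8% of patients are 12%, 20% and 32% of all primary events at a 25% rate (3/25, 5/25, 8/25).

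**The other direction**

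Suppose the planned effect is real and a fraction m of the call-only events is missed in the continuation arm, where call-only events are a fraction f of all primary events. The recorded rate in that arm is 0.25 × (1 − f × m). With f = m = 20% it is 24.0%, the difference shrinks to 4.25 points, and power falls from 80.3% to 63.0%. With f = 5% and m = 10%, power is 78.5%, a negligible loss.

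**The case against.** **The caller may not know the arm.** The project staff are a group, and the article does not say that one individual handles the same patient before surgery and at 30 days. This stands. A reader might infer that every caller knows the arm, but the text shows only that nothing prevents it.

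**The call may collect little beyond vital status.** Outcome data are said to come from case records, diagnoses come from treating clinicians, and the 30-day window is explicit only for mortality. This also stands. If no non-fatal event is found only by the call, the bias is zero. The article does not say so, however, and case records at the centre would not ordinarily show an event treated elsewhere.

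**The call is not the only contact after discharge.** A reader might infer that it is, but Data collection and follow-up describes retrieval of missing data from patients or next of kin. The call is the only scheduled contact described, and the retrieval contact is not masked either.

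**The blinded committee already protects the endpoint.** This is half right: it protects against over-recording, not against events that were not elicited.

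**Scripts and call assignment belong in the full protocol or a manual.** That is fair for the script, and its absence is not the point. But the article itself states who makes the call and who checks allocation, and it gives both tasks to one group without separating them.

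**Masking the caller is only a partial remedy.** Patients know their arm, and project staff also take outcomes from case records unmasked. Both are true. The change improves one channel and leaves the other as it is.

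**Conclusion.** The point holds in a limited form. One staff group has both the allocation check and the 30-day call in an open-label trial, and the article neither masks nor separates the callers. Non-fatal primary events found through the call are open to unequal elicitation, and the committee cannot repair missed events.

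The size is unknown. It is close to nil for mortality, and nil overall if the call adds no non-fatal events. Under the middle assumptions (5% of patients, 20-point gap) the bias is 1.0 point and the false-positive rate about 8% against 4.8%. The 23% at the top of the range needs both extreme assumptions together. None of these inputs comes from the article, so the figures illustrate what could happen and are not an estimate. They do not support a claim that the primary result will be biased. The point justifies a cheap safeguard; it is not a defect in the sample size or the analysis.

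**What to change.** In Participants, state that each patient's 30-day call is made by an existing project-staff member at that centre who did not do that patient's preoperative allocation follow-up. Specify also:

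- a call sheet that does not show the allocation;
- one fixed script for both arms that lists the primary components the call collects, which also settles what the call is for;
- that the caller does not ask about preoperative ACEI/ARB use and records any unmasking;
- that a positive answer triggers retrieval of the relevant records for the blinded committee.

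Cost: a script, a call sheet and minor scheduling effort, with no added visits and no change to sample size or alpha. The article gives no staff numbers or budget, so it cannot be shown that the change is free. A centre with a single project-staff member could not separate the tasks and should record that the call was not masked; the fixed script would still help there. Residual unmasking will remain because patients may reveal their arm. Trial status says recruitment had not begun, so the change could precede the first patient.

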**Fig. 2 Fig2:**
[figure not shown]
Enrolled adult hypertensive patients undergoing elective major non-cardiac surgery under general or neuraxial anaesthesia over a period of 3 years

### Inclusion criteria

The following are the inclusion criteria:Patients requiring major elective non-cardiac surgery are defined as surgery with an expected duration of > 2 h from the surgical incision and/or a postoperative hospital stay of at least 3 days [8].Age 18–70 years of either gender.Patients chronically treated with ACEIs/ARBs (ideally 3 months or more or a minimum of 2 weeks at the time of randomisation).

### Exclusion criteria

The following are the exclusion criteria:Emergency surgery (surgical treatment needed within 48 h)Hyperkalaemia (serum potassium level > 5.5 mmol/L) during the preoperative visitPatients with severe chronic renal insufficiency as defined by estimated glomerular filtration rate < 15 mL/min/1.73 m^2^ or requiring renal replacement therapyPatients with preoperative shock (defined by the need for vasoactive drugs before surgery or a mean arterial pressure < 65 mmHg)Patients taking ACEI/ARBs for left ventricular dysfunction (ejection fraction < 50%)Uncontrolled preoperative blood pressures (systolic blood pressure > 180 mmHg and/or diastolic blood pressures of > 110 mmHg)

### Ethical aspects

The study was approved by the Institutional Ethics Committee of AIIMS Bhubaneswar (1 June 2020 vide letter no. T/EMF/Anesth/20/10) and by the ethics committee of each of the collaborating hospitals. Furthermore, the study was registered in the Clinical Trials Registry of India (CTRI/2021/01/030199, registered on 4 January 2021). Patients will receive written information regarding the trial, the possible risks and benefits, and an informed consent will be obtained from them by the research assistants before enrolling them into the trial.

### Randomisation and blinding

All study patients will receive the same standards of care and management, including treatment of any harm resulting from the trial. However, they will receive no compensation as a result of participation in the study. They will be randomised to either continue with their ACEI/ARB treatment (including on the day of surgery) (group A) or to withhold it 24–36 h before surgery (group B) (two doses of the ACEI or ARB will be omitted to account for variation in the timing of administration, i.e. morning or evening). The patient’s blood pressure will be monitored periodically and treated with calcium channel blockers if necessary. Other antihypertensives that the patient may be concurrently receiving will be continued on the day of surgery. All such orders will also be recorded. Following surgery, anti-hypertensive medications including ACEIs/ARBs will be restarted at the earliest and the date of restarting anti-hypertensive therapy will be noted.

Randomisation will be carried out using permuted block randomisation (blocks of 20). The randomisation codes and sequence will be computer-generated by a statistician at each institute. The randomisation codes and the sequence will be kept secure at each participating centre. One code from a block sequence will be allotted each time when the patient is enrolled into the study. Allocation concealment will be with opaque sealed envelopes which will be opened 2 days before surgery. The diagnosis of outcomes will be made by clinicians treating the patients. The data for primary and secondary outcomes will be collected from the anaesthesia and surgical case records by the investigators and the project staff. The project staff will be trained by the investigators in the aspects of data collection and approach to missing data.

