### Sample size calculation

Based on an incidence of 25% of the primary endpoint in the reference group [11], a total of 2016 patients will allow an 80% power to detect a 21% relative decrease of complications in the experimental group. To account for dropouts, a total of 2100 patients (700 at each centre) will be included. The analysis will be an intention-to-treat analysis. Since one interim analysis will be planned after recruiting 1000 patients according to the O’Brien and Fleming method, the interim alpha will be set at 0.0052 and the final nominal alpha at 0.048 (Additional file 1). The *P* values and respective sample sizes were based on a final sample size of 2100, and 1 interim analysis at halfway point was calculated using the “gsDesign” package of the R statistical software v4.0.0 (R Statistical Corp, Vienna, Austria).

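### One fixed, published block size of 20, with lists made and kept at each open-label centre, lets staff who keep count foresee some allocations; varying undisclosed block sizes would cheaply reduce this

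*Protocol article*

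**What the plan says.** Under Study design, the protocol article says that the study "is a multi-centric, open-label, randomised controlled two-arm trial". The same section fixes equal allocation to the two arms.

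Under Randomisation and blinding it sets out the scheme:
- Block size: "Randomisation will be carried out using permuted block randomisation (blocks of 20". One size is given, and nothing says that it varies or is withheld from the centres.
- Generation: "The randomisation codes and sequence will be computer-generated by a statistician at each institute".
- Custody: "The randomisation codes and the sequence will be kept secure at each participating centre".
- Use: "One code from a block sequence will be allotted each time when the patient is enrolled into the study".
- Concealment: "Allocation concealment will be with opaque sealed envelopes which will be opened 2 days before surgery".

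Under Sample size calculation, "a total of 2100 patients (700 at each centre) will be included". The Participants section has patients enrolled at the preoperative visit and project staff following them to check adherence to the allocated group. The Study design section instead places randomisation at hospital admission. The interval between enrolment and envelope opening is not given.

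**The concern.** With 10 places per arm in each block of 20, the rest of a block is determined once one arm has used its 10. Before that point, the arm that is behind is the more likely next code. Because treatment is open-label, allocations can be seen at the centre once they are revealed, and the block size is now in print. An opaque envelope hides the next card but does not stop anyone counting the earlier ones.

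The stake is selection bias at entry. Surgery is elective, so the timing of enrolment has some flexibility. The Background section says that the choice to withhold these drugs often follows individual practice, so clinicians may hold preferences. Someone who foresees the next code could enrol or defer a patient accordingly. The regression described under Statistical analysis adjusts only for measured factors. Intention-to-treat analysis and blinded adjudication do not repair selection that happened before randomisation.

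**Working it through.** **Inputs from the article.** Block size 20 and 1:1 allocation, so m = 10 places per arm. 700 patients per centre gives 700/20 = 35 blocks per centre and 3 × 35 = 105 blocks overall. The planned effect is a 21% relative reduction from 25%: 0.21 × 25 = 5.25 points.

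**The plan's own figure.** The article gives no figure for predictability. Its sample size does reproduce: 25% versus 19.75% with 80% power and two-sided alpha 0.048 needs 2002 patients, within 1% of the stated 2016, and 2016/0.96 = 2100. This point does not alter those numbers.

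**Step 1: certain codes when every earlier allocation is known.** A code is certain once one arm is full, so the number of certain codes equals the length of the final run in the block. Its mean is 2m/(m+1) = 20/11 = 1.82 per block.
- Share: 1.82/20 = 9.1%.
- Per centre: 35 × 1.82 = 64 of 700.
- Overall: 105 × 1.82 = 191 of 2100. Of these, 105 are simply the last code of each block.

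**Step 2: guessing when the code is not certain.** Always guessing the arm with fewer allocations so far, and tossing a coin at ties, is right on average 12.34 times in 20, or 61.7%, against 50% by chance.

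**Step 3: earlier envelopes still sealed.** Suppose L earlier envelopes are unopened when the next patient is enrolled. A code is then certain only if it, the L codes before it and all codes after it in the block belong to one arm. The expected number per block is the sum over r = L+1 to 10 of 2·C(20−r, 10)/C(20, 10). For guessing, the count at position k uses only the first max(0, k−1−L) codes of the block.

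**Step 4: possible size of the bias.** Assume that staff act on the guess so that the mean risk of enrolled patients differs by 2 points between the two guesses. If the guess is right with probability p, the expected baseline difference between arms is 2 × (2p − 1) points. With p = 0.617 this is 2 × 0.234 = 0.47; with p = 0.552 it is 2 × 0.104 = 0.21.

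| Unopened (assumed) | Certain per block | Certain of 2100 | Share certain | Guess right | Baseline difference (points) | Share of 5.25 |
|---|---|---|---|---|---|---|
| 0 | 1.82 | 191 | 9.1% | 61.7% | 0.47 | 9% |
| 1 | 0.82 | 86 | 4.1% | 59.2% | 0.37 | 7% |
| 3 | 0.13 | 14 | 0.7% | 56.8% | 0.27 | 5% |
| 5 | 0.015 | 2 | 0.07% | 55.2% | 0.21 | 4% |

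For scale, 700 patients per centre over 3 years is 700/156 = 4.5 per week. A one-week gap between enrolment and opening (assumption) would leave about 4 to 5 envelopes sealed. If enrolment and opening fall close together, the top rows apply.

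**Step 5: effect of varying the block size.** By simulation, with sizes drawn at random from 16, 20 and 24, and with an observer who knows the possible sizes, where each block starts and every earlier code, the certain share falls from 9.1% to about 3.0%. Small varying blocks do not help: sizes 4, 6 and 8 give 8.9%.

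**The case against.** The strongest reply is that the protocol already does much of what is wanted. Twenty is a large block: a fixed block of 4 would make 33% of codes certain and a block of 6 would make 25% certain. Centre-specific lists are the natural reading, the envelopes are opaque and sealed, and opening is delayed until 2 days before surgery. That delay matters, because patients enrolled earlier may still hold sealed envelopes, and with five of them almost no code is certain. This stands. It makes 191 an upper bound, but guessing remains above chance in every row of the table.

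A second reply is that nothing in the article says enrolling staff keep a centre-wide tally or know where blocks begin. That is also fair. The figures describe what a person who keeps count could know, not what anyone will do. The 2-point difference in risk has no support in the documents and only illustrates scale.

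A third reply is that the list is held by a statistician and described as secure. A reader might infer from on-site storage that recruiting staff can look up the sequence. The documents do not support that: no passage gives them access. On-site custody is the lesser part of the risk.

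It might also be said that an article leaves such detail to the full protocol. Who prepares and holds the envelopes may well be described there. But the block size, its publication, and where the list is made and kept are stated here, so the point does not rest on an omission.

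**Conclusion.** The point holds as a modest, avoidable weakness in concealment. A single disclosed block size in an open-label trial leaves between about 2 and 191 of 2100 codes certain, and correct guessing between 55% and 62%, depending on how many earlier envelopes are still sealed (5 down to 0). Under the assumed 2-point difference in enrolled risk between guesses, the baseline difference would be 0.2 to 0.5 points, or 4% to 9% of the planned 5.25.

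Two stronger readings should be avoided. One takes 191 as the expected number; it requires every earlier allocation to be known at enrolment, which the delayed opening makes doubtful. The other puts the bias at nearly 1 point, or 18% of the planned effect: 4 × 0.234 = 0.93. That needs risk to move up 2 points on one guess and down 2 on the other, a 4-point swing, at every unbalanced count, with no envelope outstanding. Nothing in the documents supports either.

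The calculations assume one unbroken list per centre and an observer who tracks block boundaries. The sample size and error rates are unaffected. The importance is minor to moderate.

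**What to change.** Before the first patient is enrolled:
- Replace the fixed blocks with randomly varying, moderate-to-large block sizes within each centre. Sizes 16, 20 and 24 illustrate the gain, a fall in certain codes to about 3.0%; small blocks should be avoided.
- Do not disclose the new sizes to the centres, or in publications while recruitment is open. The protocol can say that sizes vary and are held by the coordinating-centre statistician.
- Have that statistician generate and hold all three lists and prepare the sealed envelopes away from the recruiting centres.
- State at which step the code is allotted and at which the envelope is opened, so that the enrolment-to-opening interval is clear and the Participants, Study design and Randomisation sections agree.

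The cost is new lists, off-site envelope preparation and an amendment. The Trial status section reports that recruitment has not begun, and the article already refers to a trial coordination centre, so the set-up effort is small. After enrolment starts, the change could protect only later patients.
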